### Data analysis plan

#### Descriptive analysis

Descriptive information about the sample population will be provided. This will include the distribution of the relevant characteristics of study patients, including demographic data, the distribution of candidate predictors, the ranges of continuous predictors and the amount of missing data (with possible reasons for the missingness). This is to permit an assessment of the context, case mix and setting of the study; the ranges of continuous predictors that are compatible with the MOAT; and the potential impact of any missing data. Descriptive information will also be provided on the proportion of patients with MRPs, including the severity and preventability. We will also report the outcome frequency (namely patients with at least one MRP that is moderate or severe and preventable) across the predictor categories.

#### Statistical analysis

The data analysis plan has been developed prior to any analysis of the study data to prevent the potential for data-driven model development and type 1 errors.^47^ The study method is informed by the recommendations of the PROGRESS partnership^42 44 47 48^; however, it is recognised that a prognostic research protocol cannot be a ‘rigid blueprint’. Peat *et al*
43 state that it is neither possible nor desirable to prespecify all analysis. We therefore acknowledge that it may be necessary to modify the analysis plan or carry out additional analyses in light of new findings. Analysis will be conducted using SPSS V.24.

#### Missing data

Complete-case analysis can lead to selection bias^55 68^ and loss of statistical power/precision.^61^ We will therefore examine missing data to establish the missingness mechanism, and if we can establish that the data are ‘missing at random’ we will use multiple imputation (using ≥20 imputed data sets) to impute the missing values. We will then carry out complete-case analysis and compare the results with those from multiple imputation to assess for potential bias due to data that are ‘missing not at random’.

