#### Model building

We will use multivariable logistic regression modelling to develop the MOAT. This has been chosen as the outcome is binary, and all participants will be followed up to the end of the study period. The aim is to produce a parsimonious model to increase clinical applicability while retaining reasonable predictive performance.

Backwards elimination will be used to reduce the set of candidate predictors. The Akaike Information Criterion (AIC) will be used to exclude predictors. We chose to use the AIC due to the relatively small data set (hence relatively larger p values for the predictors), as it is less likely to result in underfitting than alternative methods.^69^

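### Imputation is conditional on establishing missing at random, which data cannot do, and the complete-case comparison cannot diagnose missing-not-at-random bias

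*Protocol article*

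**What the plan says.** The Missing data section starts from a sound position: "Complete-case analysis can lead to selection bias", and it also costs precision. It then sets a condition, introduced by "We will therefore examine missing data to establish the missingness mechanism, and if we can establish that the data are"; the state to be shown is MAR. When the condition is met, the plan is that "we will use multiple imputation (using ≥20 imputed data sets) to impute the missing values". It does not say what happens if MAR cannot be established.

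The section ends with a check aimed at MNAR data: "We will then carry out complete-case analysis and compare the results with those from multiple imputation to assess for potential bias due to data". No other analysis of departures from MAR is mentioned.

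Elsewhere, the Descriptive analysis section promises to report "the amount of missing data (with possible reasons for the missingness". The Statistical analysis section allows the plan to be modified and further analyses added. The analysis model is a logistic regression (Model building section), whose coefficients later become the simplified score.

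**The concern.** Two statements do not do the work assigned to them.

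First, the choice of primary method depends on a finding that the data cannot deliver. Observed data can count against missing completely at random. They cannot separate MAR from MNAR. If 'establish' is softened to 'judge plausible', the primary method still depends on an undefined judgement made after seeing the data, in a plan published to prevent data-driven development.

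Second, the comparison is given an interpretation it cannot carry. Complete-case analysis and imputation rest on different conditions. They can differ when imputation is valid and nothing is MNAR, and they can agree when both are biased. A reader of the results could draw the wrong conclusion either way, and the affected coefficients feed the MOAT score.

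Outcome-related missingness is conceivable here, though this is inference and not stated. Body mass index and laboratory values are the first documented results after admission, while medication-related problems accrue until discharge. A longer stay therefore gives more chance both of a recorded value and of an event.

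**Working it through.** **1. The plan's own figures.** Events: 1500 × 0.32 = 480. Events per variable: 480/37 = 12.97, stated as 13. Half-width for 90% sensitivity: 1.96 × √(0.9 × 0.1/480) = 0.027, stated as ±3%. All reproduce. The Missing data section gives no figure except the number of imputations (at least 20).

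**2. Why MAR cannot be established.** Let R indicate that a value is observed. MAR says P(R | observed, unobserved) = P(R | observed). Testing this needs the unobserved values.

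**3. Why the comparison is not diagnostic.** Among complete cases (R = 1),

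logit P(Y=1 | x, R=1) = logit P(Y=1 | x) + log[P(R=1 | x, Y=1) / P(R=1 | x, Y=0)].

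The last term biases complete-case estimates whenever missingness depends on the outcome, under MAR or MNAR. Imputation removes it only under MAR.

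**4. Illustration by simulation.** From the plan: N = 1500, prevalence 32%, 20 imputations. Assumed: y is Bernoulli(0.32); x2 is N(0.5y, 1) and complete; x1 is N(0.4y, 1), partly missing, and independent of x2 given y. True intercept and log odds ratios for x1 and x2: −0.960, 0.401, 0.502. Imputation is by normal regression on y and x2, with 300 replicates. Row 5 is a variant in which x1 and x2 have correlation 0.4 given y (truth −0.904, 0.239, 0.406).

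Entries are intercept / x1 / x2; CC = complete case, MI = multiple imputation.

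| Row | Logit of P(x1 missing) | Missing | CC bias | MI bias | MI − CC |
|---|---|---|---|---|---|
| 1, MAR | −1.0 − 1.5(y − 0.32) − x2 + 2·y·x2 | 34% | 0.382 / 0.004 / −0.516 | −0.001 / 0.003 / 0.001 | −0.384 / 0.000 / 0.517 |
| 2, MAR | −1.6 + 1.6y | 27% | −0.525 / 0.004 / 0.005 | −0.008 / 0.003 / −0.001 | 0.518 / 0.000 / −0.006 |
| 3, MNAR | −1.2 + 0.6·x1·(2y − 1) | 26% | 0.001 / −0.297 / −0.001 | 0.064 / −0.297 / −0.003 | 0.064 / 0.000 / −0.002 |
| 4, MNAR | −1.0 + 1.2·x1 | 34% | −0.004 / 0.000 / −0.001 | 0.128 / −0.002 / −0.002 | 0.133 / −0.002 / −0.002 |
| 5, MNAR, correlated | −1.2 + 1.5·x1·(2y − 1) | 33% | −0.004 / −0.860 / 0.000 | 0.068 / −0.859 / 0.292 | 0.072 / 0.001 / 0.291 |

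Hand checks with the formula in step 3:
- Row 1, x2 slope at zero: −expit(−2.02) − expit(−0.52) = −0.117 − 0.373 = −0.49 (simulated −0.516).
- Row 2, intercept: log(0.500/0.832) = −0.51 (simulated −0.525).
- Row 3, x1 slope at zero: −2 × 0.6 × expit(−1.2) = −1.2 × 0.2315 = −0.28 (simulated −0.297).

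**5. Reading the table.**
- Rows 1 and 2: a clear difference with no MNAR, and imputation is right.
- Row 3: both slopes agree while x1 loses 0.297/0.401 = 74% of its true value, so an odds ratio of exp(0.401) = 1.49 is estimated as about exp(0.104) = 1.11. The intercept differs by only 0.064, which is 1.6 times its replicate SD of 0.040.
- Rows 1 and 5: the difference on x2 is positive in both. In row 1 the complete-case value is wrong and the imputed one right; in row 5 it is the reverse. The difference does not show which analysis to believe.

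**6. How strong the mechanism must be.** Row 1 is a strong mechanism, with the x2 effect reversing by outcome. A separate check used true log odds ratios of 0.50 (x1) and 0.30 (x2), 25% missing and n = 400,000. Outcome-only MAR left the complete-case slopes at 0.50 and 0.31, with the intercept shifted by 0.28. Moderate joint dependence (log odds 0.5 on outcome, 0.5 per SD on x2) gave 0.26 for the x2 slope. Strong joint dependence (−2 on outcome, +1.5 per SD on x2) gave 0.62.

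**The case against.** The strongest reply is that the section's intent is clear and sensible. It rejects complete-case analysis at the outset, intends imputation under a plausible MAR assumption, and adds complete-case results afterwards as a secondary look. It sets no threshold, and the descriptive report of reasons for missingness will inform judgement. Much of this stands. Reporting both analyses is good practice, and the comparison is not always silent under MNAR, as row 5 shows. What does not stand is calling the comparison an assessment of MNAR bias, since the same pattern can arise under MAR.

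Three stronger readings are tempting but unsupported:
- A reader might infer that the plan falls back on complete cases if MAR is not established. It names no fallback; its only complete-case analysis comes after imputation.
- A reader might infer a rule for discarding the imputed model or declaring it safe. The section says only that results are compared.
- A reader might infer a breach of the aim of 10 events per variable. That needs complete-case analysis to become primary and more than 1 − 370/480 = 23% of patients to be incomplete, with missingness unrelated to outcome. At 30% incomplete it would be 336/37 = 9.1. The document gives no missing fraction, and it chose routinely recorded predictors to limit missingness.

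It is also fair that imputation-model contents and sensitivity analyses are often left to a fuller plan. Their absence is not the fault; the fault is the condition and the interpretation that the article itself states.

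**Conclusion.** The point holds in limited form. The stated condition for imputing cannot be satisfied from the data, and nothing is specified for when it is not. The stated use of the complete-case comparison is a wrong inference: difference does not show MNAR, and agreement does not exclude it.

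The possible size ranges from negligible to serious. Under MAR the x2 slope moved from 0.30 to 0.26 with moderate joint dependence, and by about 0.52 with strong dependence. Outcome-only MAR moved only the intercept, which still matters for calibrated risks. Under MNAR an undetected slope bias of −0.30 on 0.40 was possible. These values rest on assumed fractions of 25% to 34% and assumed mechanisms. They show that the comparison can mislead, not that it will in this cohort. The repair is cheap and should be made before the data are analysed.

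**What to change.** Replace the condition and the final sentence of the Missing data section with the following:

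- Multiple imputation is the primary analysis, with MAR as a stated working assumption and not something to be established. The imputation model includes the outcome and all candidate predictors.
- Complete-case results are reported as a supportive analysis, with no conclusion about MNAR drawn from agreement or disagreement.
- MNAR is assessed by a delta-shift: add a prespecified range of shifts to the imputed values of the predictors with most missing data, refit the final selected model, and report the change in coefficients, area under the ROC curve and calibration.

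The cost is a rewording of two sentences and one extra sensitivity analysis. Confining the shifts to the final selected model avoids repeating the backward elimination and the 200 bootstraps for each shift. The price is that the analysis does not show whether MNAR would have changed which predictors were selected, and the report should say so.

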#### Candidate predictor handling

We will first review the measurement reliability of each candidate predictor and consider excluding any that are found to be unreliable.^55^ We will also consider if there are any closely related predictors that may need to be combined, or one excluded from the analysis.^55^ All candidate predictors that are measured as continuous variables will be analysed on their continuous scale, that is we will not dichotomise or use categorisation as this can lead to optimistic model performance.^47 49 55 61^ We have chosen to treat liver disease as a binary variable (see table 1), but this is because of the variation in liver function tests dependent on the type and stage of disease, and to be consistent with pharmacy prioritisation tools currently in use in the UK.^28^ Individual continuous predictors will be examined to identify/investigate unexpected values in order to establish if they are recording errors or true outliers. We will also check for linearity of continuous predictors and use appropriate data transformation if required.^69^ For categorical variables we will review the number of patients within each group and consider the need to collapse groups if there are insufficient patients to permit robust modelling.^61^

#### Model building

We will use multivariable logistic regression modelling to develop the MOAT. This has been chosen as the outcome is binary, and all participants will be followed up to the end of the study period. The aim is to produce a parsimonious model to increase clinical applicability while retaining reasonable predictive performance.

Backwards elimination will be used to reduce the set of candidate predictors. The Akaike Information Criterion (AIC) will be used to exclude predictors. We chose to use the AIC due to the relatively small data set (hence relatively larger p values for the predictors), as it is less likely to result in underfitting than alternative methods.^69^

#### Adjusting for optimism

The predictive performance of prognostic models is overestimated when assessed using the same sample data used in development (known as the apparent performance), simply because the model has been optimised for that data. To account for this ‘optimism’, we will assess the predictive performance of our original model using bootstrap validation. Steyerberg^69^ advises that 100–200 bootstraps may be sufficient; therefore, we plan to use 200, but will increase this if it is needed to achieve a stable estimate. We can then use this to calculate a ‘shrinkage factor’, which will be used to adjust our original model to produce the final model/MOAT.

#### Creating a simplified scoring system

The final prognostic model will be used to develop a simplified scoring system or ‘clinical decision rule’. These differ from prognostic models in that they indicate a specific course of action, rather than simply providing an estimate of risk, and have the advantage that they are simpler to use in clinical practice as they do not require complex calculations.

We will use the method developed by Sullivan *et al*
70 to convert the regression coefficients from the final prognostic model into a score. We will then create ‘risk groups’ (high, medium and low) based on the scoring system.

The development of the scoring system for the MOAT will require categorisation of the continuous predictors and the selection of appropriate cut-off points for the risk categories; we will therefore seek input from clinical experts to ensure that the grouping is clinically practical and appropriate.

#### Assessing model performance

We will assess the predictive performance of the final prognostic model using calibration (agreement between observed and expected predictions) and discrimination (the ability to differentiate between those who do or do not experience the outcome event). The calibration will be presented as a graph of the predicted risk of experiencing a preventable, moderate or severe MRP versus the observed risk in the study sample. Discrimination will be reported as the area under the receiver operating characteristic curve.

The predictive performance of the simplified MOAT scoring system will be reported using the classification measures: sensitivity and specificity.

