#### Sample size calculation

Sample size is often calculated based on significance testing (power calculations), but this is not straightforward for prognostic modelling studies as there is often not a clear ‘measure of effect’ to power the research. An alternative method is to calculate the sample size based on the desired precision of a sample estimate.^55^ An alternative approach that is commonly used is the ‘rule of thumb’ of '10 events per variable’ (EPV).^66^ This method requires the sample size to be based on the prevalence of the outcome measure and the number of candidate predictors that will be used in model development.^49 54 55 66^ Although there is debate over the optimal number of EPV, with recognition that ‘the rule of 10 or more EPV is not a well-defined bright line’,^64^ there is agreement that models developed with less than 10 EPV need to be interpreted with caution.^55 64^ The reason for the potential problem with using less than 10 EPV relates to the reliability of the model when used in a new group of patients. If a model is too closely adapted to the developmental data, it can reflect associations between the candidate predictors and outcome which are due to chance rather than true associations, known as ‘overfitting’ or ‘optimism’.^49 55 61^

For this study the sample size has been dictated by practical considerations (funding, time available and accessibility of data at the study sites), resulting in the capacity to include 1500 (1000 from Hospital A and 500 from Hospital B), plus an additional 10% per site to allow for exclusion of patients who do not meet the eligibility criteria. We have therefore used both the precision and EPV methods to consider the adequacy of this sample size, based on an estimation of the outcome prevalence in the study population.

The outcome of interest for this study is moderate or severe, preventable MRPs in hospitalised UK patients. No estimate for the prevalence of this outcome currently exists, but Blix *et al*

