51 (Norway 2004) reported that 81% of 827 hospitalised patients experienced an MRP, with approximately half of all MRPs classified as ‘extremely important’ or ‘major’ in terms of clinical significance (preventability not reported). To establish the prevalence of the outcome in the study population, we carried out pilot work involving 200 patients, and found that 39% (95% CI 32% to 45%) experienced at least one moderate or severe, preventable MRP (using the proposed visual analogue scale for medication errors and a severity score of 3 or more). Although this is consistent with Blix’s work, we recognise that our estimate is based on a small sample of patients (200). In addition the MRPs were severity rated by three members of the expert panel rather than the four proposed for the main study. We have therefore chosen to use the lower CI limit as an estimate of the outcome prevalence, that is, 32%. Given an anticipated outcome prevalence of 32% and a sample of 1500 patients, we anticipate identifying 480 patients with at least one moderate or severe preventable MRP.

To consider the adequacy of the sample size using the precision method, we first established acceptable target sensitivity for the MOAT by including a question in our survey of healthcare professionals and patient/public representatives, detailed above. We proposed a target sensitivity of 90% and asked survey respondents if this was acceptable. This sensitivity was selected based on previous research to develop a ‘clinical decision rule’ to identify emergency department patients at risk of adverse drug events.^67^ Hohl *et al*
67 used a target sensitivity of 90% as this was deemed acceptable by emergency physicians and considered feasible for implementation in terms of workload for pharmacists. A total of 237 responses were received for this question: 189 (80%) answered that 90% was an acceptable target, 21 (9%) answered no and 27 (11%) were ‘unsure’. As a result we concluded that 90% is an acceptable target for sensitivity. Given the anticipated number of study outcomes and a target sensitivity of 90%, this will permit the precision of the sensitivity to be estimated with 95% CIs of ±3%, which we consider to be an acceptable level of precision in terms of clinical usefulness of the MOAT.

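### The optimism correction stops at the regression model, so the simplified score's sensitivity and specificity are reported uncorrected

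*Protocol article*

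**What the plan says.** Under Adjusting for optimism, the article states that apparent performance is too favourable because the model was fitted to the same data. The remedy is: "we will assess the predictive performance of our original model using bootstrap validation", using 200 resamples or more if needed. The resulting shrinkage factor is applied to that model to give the final one.

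The next section, Creating a simplified scoring system, converts the final model's coefficients to points and forms three risk groups. It notes that this requires "categorisation of the continuous predictors and the selection of appropriate cut-off points for the risk categories", with input from clinical experts.

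Assessing model performance gives calibration and the area under the ROC curve for the final model. For the score it says: "The predictive performance of the simplified MOAT scoring system will be reported using the classification measures: sensitivity and specificity". It mentions no resampling or other validation there.

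Under Sample size calculation, the target sensitivity is 90%. On the expected number of events, "this will permit the precision of the sensitivity to be estimated with 95% CIs of ±3" per cent. Prospective validation in a new cohort appears under Future plans, outside this study.

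**The concern.** The score is the form of the tool meant for simple use in practice, and the 90% sensitivity target is one of the two arguments for the sample size. Yet the correction is described for an object one step upstream of the score. Predictor selection and points both come from the study patients' outcomes. If the score is then evaluated on those patients without correction, its sensitivity and specificity will tend to be too high, for the reason the article itself gives.

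The article makes the follow-on research depend on good predictive performance, so a flattering figure bears on that decision. There is a related gap. Three risk groups have two boundaries, and sensitivity needs one of them to define a positive result. The article does not say which boundary the 90% target belongs to.

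**Working it through.** **1. The plan's own precision figure.** The inputs, all from Sample size calculation, are 1500 patients, prevalence 32% (lower pilot confidence limit) and target sensitivity 90%.

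- Events: 1500 × 0.32 = 480, as stated ("we anticipate identifying 480 patients with at least one moderate or severe preventable MRP").
- Half-width: 1.96 × √(0.9 × 0.1 / 480) = 1.96 × 0.01369 = 0.0268, or 2.7 points. This rounds to the stated ±3%.
- Wilson interval: 87.0% to 92.4%. Clopper-Pearson interval: 87.0% to 92.5%.
- Events needed for exactly ±3 points: 1.96² × 0.09 / 0.03² = 384.2, so 385. The plan has margin.

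The figure is reproduced. The formula treats the rule as fixed before these 480 patients were seen. It has no term for selecting predictors, deriving points or choosing a cut-off on the same patients.

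**2. Does shrinkage carry the correction into the score?** Write the linear predictor as a + Σ bⱼxⱼ. Shrinking by a common factor s > 0 gives a′ + s Σ bⱼxⱼ. Two patients ordered one way before are ordered the same way after. If points are coefficients divided by a common unit that is itself taken from the coefficients, s cancels. If the unit is fixed, s changes only the rounding. Shrinkage corrects predicted risks that are too extreme. It does not lower sensitivity or specificity at a cut-off chosen on the score.

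**3. Possible size.** The article gives no expected AUC or coefficients, so the size can only be shown under assumptions. The simulation used:

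- 1500 patients, prevalence 32%, and 37 independent candidates (12 continuous, 25 binary), of which 11 had true effects
- backward elimination while the smallest Wald chi-square was below 2, as a stand-in for AIC
- four categories per continuous predictor with edges fixed in advance, and rounded points
- no shrinkage factor, for the reason in step 2
- cut-off at the highest score with apparent sensitivity of at least 90%
- 300 data sets per scenario, each score then applied to 100,000 new patients

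| True-model AUC | 0.65 | 0.70 | 0.77 |
|---|---|---|---|
| Mean apparent sensitivity | 92.3% | 91.7% | 91.3% |
| Mean sensitivity in new patients | 90.2% | 89.9% | 90.0% |
| Optimism in sensitivity (points) | 2.1 | 1.8 | 1.3 |
| Optimism in specificity (points) | 0.9 | 0.6 | 0.8 |
| Naive 95% interval covers new-patient sensitivity | 57% | 67% | 85% |

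Every failure to cover was an overestimate. The Monte Carlo standard error of the coverage figures is about 2 to 3 points, for example √(0.57 × 0.43 / 300) = 0.029.

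**The case against.** **The ±3% is right.** A reader might infer that the promised precision is not delivered. It is: the arithmetic holds, with margin, and the article uses it to judge whether a sample size set by practical limits is adequate. The problem is an estimate centred too high, with coverage lost as a result.

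**Outcome-tuned cut-offs are not described.** A reader might infer that categories and cut-offs are fitted to the outcomes. The article says only that clinical experts will have input. Edges and cut-offs set without sight of outcomes would give less optimism than the table, which tunes the cut-off. This limits the size but does not remove the point, because selection and points still come from these patients and the article does not say that cut-offs are chosen blind to outcomes.

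**A falsely met target is not shown.** Mean new-patient sensitivity was 89.9% to 90.2%, so on average the target was essentially met. It fell below 90% in 41%, 48% and 47% of data sets in the three scenarios, but that follows from the tuned cut-off, which the article does not describe.

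**The target is not meaningless.** Sensitivity can be reported at both boundaries. What is missing is the link to the 90%.

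**Containment.** External validation is required before routine use, which limits the harm but does not make this study's figures unbiased.

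**Condensed article.** The Abstract says that bootstrapping will adjust the tool for optimism, and a fuller plan might cover the score. However, the article sets out its own data analysis plan, published so that the analysis is specified in advance, and there the bootstrap is defined for the regression model.

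**Conclusion.** The point holds in limited form. As written, the correction covers the regression model, and the score's sensitivity and specificity are reported without one. Evaluation on the same 1500 patients is an inference, though a strong one: there is one cohort, and a new one is left to future work. The direction of the bias follows from the article's own premise. Its size does not. The 1.3 to 2.1 points and the 57% to 85% coverage rest on assumed AUCs, independent predictors and a tuned cut-off, none of which the documents give. Against a half-width of 2.7 points, optimism of that order would matter for how the score is reported. This is an inexpensive improvement, and it does not undermine the sample size or the design.

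**What to change.** In each bootstrap sample, repeat predictor selection, coefficient estimation, point assignment and any categorisation or cut-off choice that uses the data. Category edges set by the clinical experts can be fixed in advance and applied unchanged. Score each resampled rule in its own bootstrap sample and in the original sample, and subtract the average difference from the apparent values.

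Report optimism-corrected sensitivity and specificity with bootstrap confidence intervals at both risk-group boundaries, and state which boundary the 90% target refers to. That choice belongs to the study team and its clinical experts.

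In Sample size calculation, describe ±3% as sampling precision for a fixed rule with 480 events.

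The cost is plan wording and extra scripting, with no new data. The article already allows more than 200 resamples if needed for stability. Reported sensitivity will probably be slightly less favourable and its interval wider.
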